### 6.1.2 Atezolizumab – Immune-mediated Adverse Events

Given the mechanism of action of atezolizumab, events associated with inflammation and/or immune-mediated AEs have been closely monitored during the atezolizumab clinical program. These include potential dermatologic, hepatic, endocrine, and respiratory events as well as events of hepatitis/elevated liver function tests (LFTs) and influenza like illness that are considered potential adverse drug reactions associated with atezolizumab.

The Adverse Events of Special Interest for atezolizumab are:

- ◆ Pneumonitis
- ◆ Hypoxemia
- ◆ Colitis
- ◆ Endocrinopathies: diabetes mellitus, pancreatitis, adrenal insufficiency, hypo- or hyperthyroidism
- ◆ Vasculitis
- ◆ Hepatitis
- ◆ Transaminitis: Grade  $\geq 2$ , (AST or ALT  $> 3\times$  ULN and bilirubin  $> 2\times$  ULN) or AST/ALT  $> 10\times$  ULN
- ◆ Systemic Lupus Erythromatosus
- ◆ Guillain Barre Syndrome
- ◆ Skin reactions: vitiligo, pemphigus
- ◆ Events suggestive of hypersensitivity, cytokine release, influenza like illness, SIRS, or infusion reaction syndromes

### 6.1.3 Atezolizumab – Safety in combination with chemotherapy

Study GP28328 is a 5 arm Phase Ib trial of the safety and pharmacology of atezolizumab administered with bevacizumab and/or chemotherapy in patients with advanced solid tumors. Arms C, D, and E are evaluating MDPL3280A administered q3w in chemotherapy naïve non-small cell lung cancer (NSCLC) patients in combination with carboplatin and paclitaxel, carboplatin and pemetrexed, and carboplatin and nab-paclitaxel, respectively. As of 10 May 2014, preliminary safety data are available from 90 treated patients. Of these patients, 88 (98%) reported one or more AEs; the majority of the events were Grade 1 and 2 in severity. The five most commonly reported AEs were fatigue, nausea, diarrhea, decreased appetite, and pyrexia. No additive adverse effects have been observed to date when atezolizumab was administered in combination with either bevacizumab or chemotherapy.

#### **6.1.4 Atezolizumab – Administration**

The dose of atezolizumab is 1200 mg flat dose on day 1 of a 3-week cycle. Atezolizumab is administered i.v. before the carboplatin infusion. Atezolizumab will be delivered in 250 ml NaCl 0.9%. No premedication is administered. The initial cycle will be given in 60 minutes, and the subsequent infusions in 30 minutes. When atezolizumab is administered as monotherapy, a visit window of +/- 5 days is allowed.

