#### **6.3.1 Atezolizumab dose modification and management of specific adverse events**

There will be no dose reduction for atezolizumab in this study. Patients may temporarily suspend study treatment if they experience an adverse event that requires a dose to be held. If atezolizumab is held because of adverse events for  $> 42$  days beyond the last dose, then the patient will be discontinued from atezolizumab treatment and will be followed for safety. If, in the judgment of the investigator, the patient is likely to derive clinical benefit from resuming atezolizumab after a hold  $> 42$  days, study drug may be restarted with the approval of the PI.

If a patient must be tapered off steroids used to treat adverse events, atezolizumab may be held for  $> 42$  days until steroids are discontinued or reduced to prednisone dose (or dose equivalent)  $\leq 10\text{mg/day}$ . The acceptable length of interruption will depend on agreement between the investigator and the PI.

Dose interruptions for reason(s) other than adverse events, such as surgical procedures, may be allowed by PI approval. The acceptable length of interruption will depend on agreement between the investigator and the PI.

Toxicities associated or possibly associated with atezolizumab treatment should be managed according to standard medical practice. Additional tests, such as autoimmune serology or biopsies, may be used to determine the etiology. Discontinuation of atezolizumab may not have an immediate therapeutic effect and, in severe cases, immune-mediated toxicities may require acute management with topical corticosteroids, systemic corticosteroids, mycophenolate, TNF $\alpha$  inhibitors, or tacrolimus. Further administration of atezolizumab will depend on whether the potential benefits of therapy outweigh the potential risks. Atezolizumab should be permanently discontinued in patients with life-threatening, immune-mediated adverse events. The following sections provide guidance for handling specific adverse events.

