### 6.3.1.10 Infusion-Related Reactions

No premedication is indicated for administration of cycle 1 of atezolizumab. Patients who experience an infusion-related-reaction (IRR) with cycle 1 of atezolizumab may receive premedication with antihistamines or antipyretics/analgesics (e.g. acetaminophen) for subsequent infusions. See table 9 for further advice.

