**Table 9 Management Guidelines for Infusion-Related Reactions**

| Infusion Reactions | Management                                                                                                                                                                                                                                                                                                                                                                                                                                                                                                  |
|--------------------|-------------------------------------------------------------------------------------------------------------------------------------------------------------------------------------------------------------------------------------------------------------------------------------------------------------------------------------------------------------------------------------------------------------------------------------------------------------------------------------------------------------|
| Grade 1     | 
 
• Reduce infusion rate to half the rate being given at the time of onset.
 
• Once the event has resolved, the nurse should wait for 30 minutes while delivering the infusion at the reduced rate.
 
• If tolerated, the infusion rate may then be increased to original rate.
 
                                                                                                                                                              |
| Grade 2     | 
 
• Interrupt atezolizumab infusion
 
• Administer aggressive symptomatic treatment
 
• Restart only after the symptoms have adequately resolved to baseline grade
 
• The infusion rate at restart should be half of the infusion rate that was in progress at the time of the onset of the IRR
 
• At next cycle, administer oral premedication with antihistamine and anti-pyretic and monitor closely for infusion reaction
 
 |

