| Grade 3-4   | 
 
• Stop infusion
 
• Proper medical management which may include oral or IV antihistamine, anti-pyretic, glucocorticoids, epinephrine, bronchodilators, and oxygen
 
• Discontinue atezolizumab and contact PI if atezolizumab is discontinued.
 
                                                                                                                                                                                              |

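### Section 6.1.4 shortens the second infusion to 30 minutes even after a grade 1-2 reaction to the first, so the only written time for cycle 2 doubles the scheduled rate for that patient

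*Protocol*

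**What the plan says.** Section 6.1.4 of the protocol sets a flat dose of 1200 mg in 250 ml every three weeks and states: "The initial cycle will be given in 60 minutes, and the subsequent infusions in 30 minutes". No tolerance condition is attached. Section 6.3 rules out reducing the dose, so infusion time alone determines the average rate.

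Reactions are handled in section 6.3.1.10 and Table 9:

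- **Grade 1, same infusion:** "Reduce infusion rate to half the rate being given at the time of onset". Once the event has resolved, the reduced rate is kept for 30 minutes, and then: "If tolerated, the infusion rate may then be increased to original rate". The row has no line for the next cycle.
- **Grade 2, same infusion:** the infusion is interrupted and symptoms are treated. After recovery to baseline, "The infusion rate at restart should be half of the infusion rate that was in progress at the time of the onset of the IRR".
- **Grade 2, next cycle:** "At next cycle, administer oral premedication with antihistamine and anti-pyretic and monitor closely for infusion reaction". No rate or time is given.
- **Grade 3-4:** "Discontinue atezolizumab and contact PI if atezolizumab is discontinued".
- **Any reaction in cycle 1 (text above the table):** patients who react "with cycle 1 of atezolizumab may receive premedication with antihistamines or antipyretics/analgesics" at later infusions. This is optional, and again no time is given.

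Two more general provisions apply. Section 6.3.1 says: "Toxicities associated or possibly associated with atezolizumab treatment should be managed according to standard medical practice". Section 4.2 says that precautions are taken for reactions of grade 2 or higher and that the sponsor and investigator discuss other options if these are not enough. Neither sets a rate or a time.

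**The concern.** Table 9 uses the infusion rate to control a reaction. It halves the rate at grade 1, restarts at half the rate at grade 2, and after grade 1 allows even the original rate again only if the patient tolerates it. Section 6.1.4, followed as written, moves the other way at the next cycle: a patient who reacted to the slow first infusion is scheduled for a faster second one.

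What is at stake is individual patient safety and uniform practice. The trial is planned for the Netherlands Cancer Institute and three academic hospitals (section 9.3), and section 6.1.2 lists events suggestive of infusion reaction syndromes among the adverse events of special interest. An investigator who keeps a reactor at 60 minutes, the cautious choice, departs from the literal text of section 6.1.4, so sites may handle the same patient differently.

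**Working it through.** **Inputs.** Dose 1200 mg, volume 250 ml, first infusion 60 minutes, all later infusions 30 minutes (section 6.1.4); halving of the rate after a grade 1 or 2 reaction (Table 9). The protocol states times, not rates, so there is no stated rate to reproduce. A constant rate over the scheduled time is assumed.

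**Scheduled rates** (rate = amount / time)

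- First infusion: 1200 / 60 = 20 mg/min (250 / 60 = 4.2 ml/min).
- Later infusions: 1200 / 30 = 40 mg/min (250 / 30 = 8.3 ml/min).
- Ratio: 40 / 20 = 2.0.

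**Patient with a grade 1-2 reaction at the first infusion**

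| Step | Rate | Relative to scheduled first infusion |
|---|---|---|
| Scheduled first infusion | 20 mg/min | 1.0 |
| After halving under Table 9 | 20 / 2 = 10 mg/min | 0.5 |
| Cycle 2 at the written 30 minutes | 40 mg/min | 2.0 |
| If a reaction recurs in cycle 2 and the rate is halved | 40 / 2 = 20 mg/min | 1.0 |

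The written cycle 2 rate is thus 40 / 10 = 4 times the reduced rate of cycle 1. Halving after a recurrence only brings the patient back to the scheduled rate of the infusion in which the first reaction occurred.

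**Patient whose first reaction is at cycle 2 or later.** The scheduled rate was already 40 mg/min and stays there, ratio 40 / 40 = 1.0. It is still 40 / 20 = 2 times the halved rate, but the schedule itself does not speed up.

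**Grade 3-4.** Atezolizumab is stopped, so there is no next infusion.

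**Search for another next-cycle time.** Sections 4.2, 6.1.4, 6.3.1 and 6.3.1.10 and Table 9 were compared. Only section 6.1.4 gives a time, and it is 30 minutes.

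**With the proposed condition.** A first-infusion reactor kept at 60 minutes would receive cycle 2 at 20 mg/min, ratio 1.0 instead of 2.0.

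**The case against.** The best defence is that section 6.1.4 describes routine administration and is a default. It also says that no premedication is given, yet section 6.3.1.10 permits premedication after a cycle 1 reaction and Table 9 directs it at the next cycle after grade 2. The reaction-specific text therefore already overrides section 6.1.4 in places. Nothing forbids a slower infusion, and standard medical practice would let a clinician use one. This stands in part. It shows that the protocol does not compel an unsafe infusion, but the override covers premedication only. On infusion time, nothing displaces the 30 minutes.

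It can also be said that the gap is narrow. Grade 2 reactors have directed premedication and close monitoring. A grade 1 reactor may already have been returned to the original rate before the first infusion ended. Both facts are correct and keep the point small. However, a grade 1 patient who tolerated a return to 20 mg/min has not been shown to tolerate 40, and after grade 1 only optional premedication and general practice apply.

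Finally, the rates measure infusion speed, not risk. That stands in full. The protocol gives neither the frequency of grade 1-2 reactions nor the chance of recurrence at 30 minutes. Table 9's slowing during a reaction does not by itself establish the right time for the next cycle.

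Two stronger readings are tempting. A reader might infer that the rate doubles after any grade 1-2 reaction; the schedule supports this only for a reaction at the first infusion. A reader might also infer that the protocol requires reactors to be infused faster or leaves them unprotected. The premedication, monitoring and standard-practice provisions do not support that.

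**Conclusion.** The point holds in a limited form. After a grade 1 or 2 reaction at the 60-minute first infusion, the only infusion time the protocol writes for cycle 2 doubles the scheduled rate, from 20 to 40 mg/min. That runs against the protocol's own approach of slowing and then returning cautiously. The conclusion rests on the fixed dose, a constant rate and a literal reading of section 6.1.4.

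The clinical size of the risk is unknown from the documents, and none is estimated here. It is partly mitigated after grade 2 and less so after grade 1. The primary endpoint, sample size and decision rule are unaffected. It is an inexpensive improvement to consider, not a flaw in the design.

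**What to change.** In section 6.1.4, allow the 30-minute infusion only if the previous infusion was tolerated without an infusion-related reaction. Otherwise keep 60 minutes, or the slower rate that the patient tolerated. Add the same next-cycle line to the grade 1 and grade 2 rows of Table 9, so that the administration and reaction sections agree.

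The cost is three short text edits. For patients with a grade 1-2 reaction, each infusion given over 60 instead of 30 minutes takes 30 minutes longer, and more if a slower rate is used. Patients without reactions are unaffected.

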#### **6.1.5 Atezolizumab - Duration of Therapy**

Treatment cycles will be repeated until progression (see definition Section 8) unless unacceptable toxicity is encountered. Patients may be treated beyond progression according to RECIST 1.1 (not according to the immune-related response criteria) under protocol-defined circumstances (see Section 8.1). At progressive disease, patients are considered off study and further systemic treatment is at the discretion of the treating physician. After 12 months of atezolizumab treatment discontinuation is allowed in case of ongoing response or stable disease. At signs of progression after discontinuation of the treatment, atezolizumab can be re-started.

### **6.2. Carboplatin**

Carboplatin is a platinum derivative and a highly polar molecule that does not readily diffuse across lipid membranes [38, 39]. In the high chloride environment of plasma, it remains largely in its native form, but once inside the cell, in which the chloride concentration is much lower, it becomes aquated and forms adducts with DNA and reacts with nucleophilic sites in a variety of targets [38]. Compared with cisplatin, carboplatin is essentially devoid of nephrotoxicity, and is less toxic to the gastrointestinal tract and less neurotoxic; by contrast, myelosuppression, principally thrombocytopenia, is dose limiting for carboplatin. Single-agent carboplatin is active in patients with previously untreated metastatic breast cancer, producing response rates of 20%-35%. [40]

#### **6.2.1 Carboplatin – Administration**

The dose of carboplatin is AUC 1.5 in a weekly schedule with a maximum of 12 cycles. This dosage has been used in the GeparSixto study in combination with liposomal doxorubicin and paclitaxel and resulted in less hematological toxicities compared to the AUC 2.0 dosage. [23] Although in most study protocols so far as well as in daily clinical practice carboplatin is used in a 3-week schedule with an AUC 4-6, we strongly feel that for the current study a weekly schedule with a dosage of AUC 1.5 will be more suitable for the following reasons: 1) while high-dose chemotherapy often depletes immune cell subsets, low-dose metronomic chemotherapy exerts a more subtle anti-angiogenic and immunomodulatory mode of action [41-43] 2) less hematological toxicities which makes it less likely that carboplatin (and atezolizumab in case of high grade or persisting toxicities) has to be withheld.

Carboplatin will be reconstituted and administered according to the standard practice in the institution. The carboplatin dose should be calculated according to Calvert's formula as follows: carboplatin dose = target AUC (GFR+25). When administered with atezolizumab, carboplatin will be administered first according to standard practice.

For the purpose of this protocol the GFR is considered equivalent to the creatinine clearance. The exact dose of carboplatin therefore depends on the GFR. The GFR can be calculated using a variety of different formulae and should be calculated as per local practice. Formulae such as the Cockcroft-Gault formula are inaccurate at the extremes of age and weight. The calculated GFR may be falsely high in obese young women and falsely low in thin elderly women. It is assumed that clinicians entering patients into this protocol will be aware of these issues and the clinical judgment of an experienced clinician should be applied to the calculation of the carboplatin dose.

We recommend capping the dose of carboplatin as follows: Using Calvert formula with capping of GFR at 125 mL/min: For a target AUC = 1.5, the maximum dose is  $1.5 \times 150 = 225$  mg

A measured GFR, using a 24-hour urine collection, is recommended if the serum creatinine is less than or equal to 53  $\mu\text{mol/L}$ , or the calculated GFR is  $<60\text{ml/min}$ . The lower of the two values of the creatinine clearance should be used to calculate dose.

If any change in GFR of more than 10% is observed, the treatment dosage should be modified accordingly.

### **6.3 Dose modification for toxicity**

- Dose reduction of atezolizumab is not permitted
- When several toxicities with different grades of severity occur at the same time, the dose modifications should be according to the highest grade observed.
- If, in the opinion of the investigator, a toxicity is considered to be due solely to one component of the study treatment (i.e., atezolizumab or carboplatin) and the dose of that component is delayed or modified in accordance with the guidelines below, the other component may be administered if there is no contraindication. This dose might be administered after the planned last dose of the chemotherapy to complete the total number of 12 administrations of carboplatin, as determined by the investigator.
- When treatment is temporarily interrupted because of toxicity caused by atezolizumab or chemotherapy the treatment cycles will be restarted such that the atezolizumab and chemotherapy infusions remain synchronized.
- If it is anticipated that chemotherapy will be delayed by  $\geq 2$  weeks, then atezolizumab should be given without the chemotherapy, if there is no contraindication.

#### **6.3.1 Atezolizumab dose modification and management of specific adverse events**

There will be no dose reduction for atezolizumab in this study. Patients may temporarily suspend study treatment if they experience an adverse event that requires a dose to be held. If atezolizumab is held because of adverse events for  $> 42$  days beyond the last dose, then the patient will be discontinued from atezolizumab treatment and will be followed for safety. If, in the judgment of the investigator, the patient is likely to derive clinical benefit from resuming atezolizumab after a hold  $> 42$  days, study drug may be restarted with the approval of the PI.

If a patient must be tapered off steroids used to treat adverse events, atezolizumab may be held for  $> 42$  days until steroids are discontinued or reduced to prednisone dose (or dose equivalent)  $\leq 10\text{mg/day}$ . The acceptable length of interruption will depend on agreement between the investigator and the PI.

Dose interruptions for reason(s) other than adverse events, such as surgical procedures, may be allowed by PI approval. The acceptable length of interruption will depend on agreement between the investigator and the PI.

Toxicities associated or possibly associated with atezolizumab treatment should be managed according to standard medical practice. Additional tests, such as autoimmune serology or biopsies, may be used to determine the etiology. Discontinuation of atezolizumab may not have an immediate therapeutic effect and, in severe cases, immune-mediated toxicities may require acute management with topical corticosteroids, systemic corticosteroids, mycophenolate, TNF $\alpha$  inhibitors, or tacrolimus. Further administration of atezolizumab will depend on whether the potential benefits of therapy outweigh the potential risks. Atezolizumab should be permanently discontinued in patients with life-threatening, immune-mediated adverse events. The following sections provide guidance for handling specific adverse events.

### **6.3.1.1 Gastrointestinal toxicity**

Immune-mediated colitis has been associated with the administration of atezolizumab. See table 1 for guidelines on how to manage gastrointestinal toxicity in patients treated with atezolizumab.

**Table 1: Dose modification guidelines for atezolizumab-associated gastrointestinal toxicity**

| Diarrhea/Colitis                                                                                                                                                                         | Management                                                                                                                                                                                                                                                                                                                                                                                                                                                                                                                                                                                                                                                                                                                                                                                                                                                                                                                                                                                                                                                                                                                                                                                                                         |
|------------------------------------------------------------------------------------------------------------------------------------------------------------------------------------------|------------------------------------------------------------------------------------------------------------------------------------------------------------------------------------------------------------------------------------------------------------------------------------------------------------------------------------------------------------------------------------------------------------------------------------------------------------------------------------------------------------------------------------------------------------------------------------------------------------------------------------------------------------------------------------------------------------------------------------------------------------------------------------------------------------------------------------------------------------------------------------------------------------------------------------------------------------------------------------------------------------------------------------------------------------------------------------------------------------------------------------------------------------------------------------------------------------------------------------|
| Grade 1                                                                                                                                                                           | 
 
Continue therapy
 
Symptomatic treatment, no steroids
 
Endoscopy should be considered if symptoms progress and/or persist for > 7 days
 
Investigate etiology: stool culture and testing for Clostridium diff, Salmonella/Shigella/Campylobacter/Yersinia (consider culture for worms/cysts/eggs)
 
                                                                                                                                                                                                                                                                                                                                                                                                                                                                                                                                                                                                                                                                                                                                                                                                                                                       |
| Grade 2
(4–6 stools/day over baseline) < 5 days                                                                                                                                | 
 
Hold atezolizumab and discontinue NSAIDs (or other medications that exacerbate colitis). Ensure adequate rehydration.
 
Investigate etiology: stool culture and testing for Clostridium diff, Salmonella/Shigella/Campylobacter/Yersinia (consider culture for worms/cysts/eggs)
 
Administer antidiarrheal agent (e.g., loperamide)
 
Consult gastroenterologist to perform endoscopy. Endoscopy+biopsies indicated if symptoms persists for >1 week. Endoscopy preferably within 48 hours after start steroids. Investigate possibility of CMV colitis (via biopsies)
 
In case of moderate/severe colitis at endoscopy; see management advice below
 
                                                                                                                                                                                                                                                                                                                                                                                                                                                                                            |
| Grade 2
(4–6 stools/day over baseline) > 5 days or recurs                                                                                                                      | 
 
Hold atezolizumab and discontinue NSAIDs (or other medications that exacerbate colitis) while etiology is being investigated
 
Consult gastroenterologist to perform endoscopy. Endoscopy+biopsies indicated if symptoms persists for >1 week. Endoscopy preferably within 48 hours after start steroids. Investigate possibility of CMV colitis (via biopsies)
 
Investigate etiology: stool culture and testing for Clostridium diff, Salmonella/Shigella/Campylobacter/Yersinia (consider culture for worms/cysts/eggs)
 
Type of immune suppression depends on severity of inflammation seen during colonoscopy:
For mild colitis (no ulcerations): start budesonide 9mg tablet once daily
For moderate-severe colitis without ulcerations: start prednisone 1mg/kg/day orally
For moderate-severe colitis with significant ulcerations (deep ulceration or ulceration >1cm): start infliximab 5mg/kg iv in combination with prednisone 1mg/kg/day orally.
 
                                                                                                                                                       |
| Abdominal pain
Blood or mucus in stool

OR

Grade 3
(≥ 7 stools/day over baseline) with peritoneal signs, ileus, or fever
OR
Grade 4 | 
 
Hold atezolizumab and discontinue NSAIDs (or other medications that exacerbate colitis)
 
Rule out bowel perforation/sepsis, consider admission in hospital for rehydration
 
Consult gastroenterologist to perform endoscopy. Endoscopy preferably within 48 hours after start steroids. Investigate possibility of CMV colitis (via biopsies)
 
Investigate etiology: stool culture and testing for Clostridium diff, Salmonella/Shigella/Campylobacter/Yersinia (consider culture for worms/cysts/eggs)
 
Type of immune suppression depends on severity of inflammation seen during colonoscopy:
For moderate-severe colitis without ulcerations: start prednisone 1mg/kg/day orally
For moderate-severe colitis with significant ulcerations (deep ulceration or ulceration >1cm): start infliximab 5mg/kg iv in combination with prednisone 1mg/kg/day orally.
 
                                                                                                                                                                                                                                                        |
| Follow-up after start therapy                                                                                                                                                     | 
After start budesonide:
In case of improvement of symptoms: treat for 4 weeks, after this treat according to symptoms, stop budesonide if free of symptoms and with mild symptoms reduce dosage of budesonide (9mg every other day). In case symptoms persist for 1-2 weeks: repeat investigations. In case no signs of infection: perform endoscopy and start prednisone 1mg/kg orally.
 
After start prednisone:
In case of improvement of symptoms: taper prednisone over a period of 4-6 weeks
 
In case no improvement after 3 days: infliximab 5mg/kg iv and continue prednisone
 
After start infliximab:
In case of improvement of symptoms: taper prednisone. After infliximab prednisone can be tapered more rapidly (<4 weeks). In case no improvement after 7 days: second administration of infliximab 10mg/kg iv. Consider a diet with only artificial food (via tube or nutritional drinks). Only water and tea without milk and sugar are allowed in this diet. In case no improvement after two cycles of infliximab: consider tacrolimus 0.1-0.2mg/kg/daily orally or 0.01-0.02 mg/kg/daily iv, under control of therapeutic levels every week.
 |
| Other advice                                                                                                                                                                      | 
 
Start antibiotics in case of fever (preference for antibiotics indicated for abdominal infections: metronidazole/ceftriaxone).
 
Only restart atezolizumab after consultation of the PI and treating physician
 
                                                                                                                                                                                                                                                                                                                                                                                                                                                                                                                                                                                                                                                                                                                                                                                                                                                                                                                                                            |

IV = intravenous; NSAID = nonsteroidal anti-inflammatory drug

